## Abstract

**Background:**

The daytime effects of insomnia pose a significant burden to patients and drive treatment seeking. In addition to subjective deficits, meta-analytic data show that patients experience reliable objective impairments across several cognitive domains. While Cognitive Behavioural Therapy for Insomnia (CBT-I) is an effective and scalable treatment, we know little about its impact upon cognitive function. Trials of CBT-I have typically used proxy measures for cognitive functioning, such as fatigue or work performance scales, and no study has assessed self-reported impairment in cognitive function as a primary outcome. Moreover, only a small number of studies have assessed objective cognitive performance, pre-to-post CBT-I, with mixed results. This study specifically aims to (1) investigate the impact of CBT-I on cognitive functioning, assessed through both self-reported impairment and objective performance measures, and (2) examine whether change in sleep mediates this impact.

**Methods/design:**

We propose a randomised controlled trial of 404 community participants meeting criteria for Insomnia Disorder. In the DISCO trial (***D***
*efining the *
***I***
*mpact of improved *
***S***
*leep on *
***CO***
*gnitive function (DISCO)*) participants will be randomised to digital automated CBT-I delivered by a web and/or mobile platform (in addition to treatment as usual (TAU)) or to a wait-list control (in addition to TAU). Online assessments will take place at 0 (baseline), 10 (post-treatment), and 24 (follow-up) weeks. At week 25, all participants allocated to the wait-list group will be offered digital CBT-I, at which point the controlled element of the trial will be complete. The primary outcome is self-reported cognitive impairment at post-treatment (10 weeks). Secondary outcomes include objective cognitive performance, insomnia severity, sleepiness, fatigue, and self-reported cognitive failures and emotional distress. All main analyses will be carried out on completion of follow-up assessments and will be based on the intention-to-treat principle. Further analyses will determine to what extent observed changes in self-reported cognitive impairment and objective cognitive performance are mediated by changes in sleep. The trial is supported by the National Institute for Health Research (NIHR) Oxford Biomedical Research Centre (BRC) based at Oxford University Hospitals NHS Trust and University of Oxford, and by the NIHR Oxford Health BRC.

**Discussion:**

This study will be the first large-scale examination of the impact of digital CBT-I on self-reported cognitive impairment and objective cognitive performance.

**Trial registration:**

ISRCTN, ID: ISRCTN89237370. Registered on 17 October 2016.

**Electronic supplementary material:**

The online version of this article (doi:10.1186/s13063-017-2012-6) contains supplementary material, which is available to authorized users.

## Background

Insomnia disorder is defined as persistent difficulties with sleep initiation and/or maintenance, resulting in significant daytime impairment. Insomnia affects approximately 10–12% of the adult population and is associated with increased risk for cardiovascular disease, depression, and early mortality [1, 2]. Daytime functioning and quality of life are known to be severely affected in those with insomnia and often drive treatment seeking [3–5]. More specifically, previous work shows that the most commonly cited areas of daytime dysfunction are problems with fatigue, work performance, cognitive functioning, and emotional regulation [6].

With respect to cognitive function, meta-analytic data indicate that patients exhibit reliable impairments (of medium effect size) in tasks probing episodic memory, working memory, and problem solving [7]. Recent, well-controlled studies also find evidence of insomnia-related impairments in switching of attention and working memory [8], and sustained attention and episodic memory [9]. These impairments are associated with global insomnia severity, sleep duration, and disturbed sleep continuity (from both sleep diaries and polysomnography). In general, neurocognitive findings are consistent with results from functional imaging studies, which reveal evidence of hypoactivation within fronto-striatal networks during task-related functional magnetic resonance imaging (fMRI) [10–13].

Despite cognitive impairment featuring in contemporary diagnostic criteria for insomnia (Diagnostic and Statistical Manual of Mental Disorders, 5th edition: DSM-5; International Classification of Sleep Disorders, 3rd edition: ICSD-3) [14], and posing significant burden to patients, there has been little evaluation of the impact of insomnia treatments on cognitive function [15]. This is surprising because cognitive impairment may drive other daytime impairments associated with insomnia (e.g. reduced work performance and increased accident risk) [6, 16]. To date, trials of Cognitive Behavioural Therapy for Insomnia (CBT-I), the first-line treatment for persistent insomnia disorder [1], have tended to employ proxy measures (e.g. general daytime functioning, work performance) or nonvalidated, single items to probe self-reported cognitive functioning as a secondary outcome [15]. No study has assessed cognitive functioning as a primary outcome. Moreover, to our knowledge only four small studies have assessed *objective cognitive performance*, pre-to-post CBT-I [10, 17–19], providing preliminary evidence that sleep improvement may be associated with improvements in complex attention and executive function. However, the largest trial to date [19] failed to observe treatment effects for delayed recall, abstract reasoning, or working memory. Thus, it remains unclear if CBT-I confers reliable improvement to cognitive performance and to what extent such improvement may be mediated by reductions in insomnia severity. If insomnia causally drives cognitive impairment then we might logically expect that (1) CBT-I improves both sleep and cognitive function, and (2) treatment effects on cognition will operate via the pathway of improved sleep.

The aim of this study, therefore, is to investigate the impact of CBT-I on cognitive functioning, assessed through both self-report and objective measures. We will recruit participants meeting criteria for insomnia disorder who also endorse cognitive complaints, and conduct a parallel-group, randomised controlled trial (RCT) of CBT-I + TAU versus wait-list control (WLC + TAU). CBT-I will be delivered online via a website and/or app [20]. Online interventions have shown robust effects on insomnia severity and self-reported sleep parameters, with effect sizes in the range of face-to-face interventions [21, 22]. Assessments, including questionnaires and computerised cognitive tasks, will also be delivered and completed fully online. This will be the first examination of the impact of digital CBT-I (dCBT-I) on self-reported cognitive impairment and objective performance in participants meeting criteria for insomnia disorder.

The primary hypothesis for the trial is:dCBT-I will reduce self-reported cognitive impairment at the end of treatment (10 weeks) relative to WLC

The secondary hypotheses are:dCBT-I will reduce self-reported cognitive impairment at follow-up (24 weeks) relative to WLCdCBT-I will improve objective cognitive performance (in the following domains: simple attention, visual attention, episodic memory, working memory, and complex processing speed), relative to WLC (10 and 24 weeks)dCBT-I will reduce insomnia severity and improve sleep efficiency relative to WLC (10 and 24 weeks)Change in insomnia severity and sleep efficiency at week 10 will mediate change in self-reported cognitive impairment and objective cognitive performance at week 24dCBT-I will lead to improvements in fatigue, sleepiness, self-reported cognitive failures, depression, and anxiety relative to WLC (weeks 10 and 24)

## Methods/design

### Research design

The study is a parallel-group, superiority RCT of dCBT-I (+ TAU) versus WLC (+ TAU). The study will be carried out completely online. Participants will be administered screening, informed consent, assessments (tasks and questionnaires), allocation to condition, and intervention through web-based platforms. Online assessment of our primary and secondary dependent variables will take place at 0 (baseline), 10 (post-treatment), and 24 (follow-up) weeks. At week 25 all participants allocated to the WLC will be offered dCBT-I to improve their insomnia (see Fig. 1 for trial design). Ethical approval has been granted from the University of Oxford Medical Sciences Inter-Divisional Research Ethics Committee (R46116/RE001) and the trial is registered at ISRCTN (ISRCTN89237370).

**Fig. 1 Fig1:**
[figure not shown]
Flow chart diagram showing summary of the trial design for the Defining the Impact of improved Sleep on COgnitive function (DISCO) study. *DSM-5 Diagnostic and Statistical Manual of Mental Disorders, version 5*, *SCI* Sleep Condition Indicator, *dCBT-I* digital Cognitive Behavioural Therapy for Insomnia, *WLC* Wait-list control

### Participants

We will recruit 404 community participants who report clinically-significant insomnia. Our inclusion criteria comprise: (a) a positive screen for probable DSM-5 insomnia disorder using items from the Sleep Condition Indicator (SCI) (scoring ≤2 on item 1 (sleep latency) *or* item 2 (wakefulness during the night) + scoring ≤2 on item 3 (frequency of disturbance) + scoring ≤1 on item 4 (sleep quality) + scoring ≤2 on daytime functioning items 5 *or* 6 + scoring ≤2 on item 8 (chronicity of problem)) [23], (b) endorsement of difficulties with concentration or memory using items from the Daytime Functioning and Sleep Attribution Scale (selecting ‘somewhat of a problem’ or ‘a very big problem’ on at least one item, when asked how much of a problem ‘difficulty concentrating and focussing on things’ and ‘difficulty remembering things’ has been in the past 2 weeks) [24], (c) being aged 25 years and above (to minimise the possibility that circadian rhythm disruption, which is common in late adolescence/early 20s, is the source of insomnia complaints), (d) having reliable Internet access at home or at work, (e) being able to read and understand English, and (f) currently living in the UK. We will screen for comorbid conditions and medication use via online survey and exclude people with (1) symptoms of a probable additional sleep disorder (e.g. possible obstructive sleep apnoea, restless legs syndrome [25]), (2) diagnosis of mild cognitive impairment or dementia, (3) psychosis or mania, (4) serious physical health concerns necessitating surgery or with a prognosis of under 6 months, (4) those undergoing a psychological treatment programme for insomnia with a health professional, (5) habitual night shift, evening, or rotating shift-workers, (6) those taking prescribed sleeping pills more than 2 nights in the past 2 weeks prior to study entry, and (7) those with suicidal ideation with intent. We will not omit participants for any other physical or mental health problems. The study will recruit through multiple channels. These include online, print and broadcast media advertisements, and the use of contact lists where adults who have agreed to be contacted about future studies will be notified about the DISCO trial. In addition to receiving free access to the dCBT-I programme, participants will also receive payment in the form of Amazon™ gift vouchers for completing each assessment point (£5 for baseline; £10 for post-treatment; £15 for follow-up).

### Randomisation and allocation concealment

This study will use simple randomisation with an allocation ratio of 1:1, as recommended for large clinical trials [26]. Randomisation will be carried out using the randomisation function within Qualtrics Survey Software (Qualtrics, Provo, UT, USA). On completion of baseline measures, each subject will be randomly assigned by the software to either dCBT-I or WLC. The research team, therefore, will be unable to influence randomisation and will have no access to future allocations.

### Blinding

Self-report assessments and performance tasks will be completed entirely online. Participants will be informed of their randomisation outcome (dCBT-I or WLC) via email, and so they will not be blind to treatment allocation. The research team, except the trial coordinator, will be blind to allocation. The trial coordinator will not be blind since they will inform participants of group allocation and monitor completion of assessments. Participant contact with the trial coordinator will be limited to scripted phrases, detailing instructions for dCBT-I access and completion of assessments, and will not cover therapy content or support. Statistical analyses will be conducted by a member of the research team who will have access to all data.

### Assessment points

Assessments will take place at weeks 0 (baseline), 10 (post-treatment), and 24 (follow-up) (see Fig. 2). Participants are advised to allow enough time to complete the questionnaires and cognitive tasks in one session, on their home computer or laptop in a quiet, distraction-free environment. On completion of the trial (week 25), all participants in the control arm will be offered access to dCBT-I. Baseline variables include demographic information such as age, gender, ethnic group, partner status, employment status, and education. Frequency of sleep medication use will also be monitored at each assessment point.

**Fig. 2 Fig2:**
[figure not shown]
Standard Protocol Items: Recommendations for Interventional Trials (SPIRIT) figure

### Intervention

dCBT-I will be delivered using the Sleepio® programme (www.sleepio.com and associated Sleepio® app) [19]. We have previously described the Sleepio® programme in two trial protocols published in this journal [27, 28]. The programme is fully automated and its underlying algorithms drive the delivery of information, support, and advice in a personally tailored manner. Delivery is structured into six weekly sessions, lasting an approximately 20 min each. The full programme can be accessed via the website or iOS app. Treatment content is based on CBT-I manuals and includes a behavioural component (sleep restriction, stimulus control, and relaxation), a cognitive component (paradoxical intention, cognitive restructuring, mindfulness, positive imagery, and putting the day to rest) and an educational component (psychoeducation and sleep hygiene) [29–31].

The programme is highly interactive, and content is presented by an animated virtual therapist (‘The Prof’). Before the start of the programme, participants complete a questionnaire to tailor the therapy and to set treatment goals. Participants complete daily sleep diary information throughout the intervention, which is used by the programme to provide tailored, personalised advice. Participants can opt to receive an email and/or SMS reminder each morning to prompt them to fill in their sleep diary. In addition, throughout the course of therapy, participants have access to an online community forum; weekly sleep expert sessions moderated by a clinical psychologist; and online library of information about sleep and sleep disorders. During weekly sleep expert sessions, users may vote on topics and submit questions to be addressed by the clinical psychologist. Questions are answered in such a way as to benefit as many people as possible and no personal medical advice is provided. Participants can view their online ‘case file’, which includes four sections: a progress review, a 'to-do' list, an agreed sleep schedule, and a list of further reading. The system provides online analytics which can be used to monitor adherence by assessing how many sessions were completed and the number of weeks to complete the course. All information gathered during the programme will be stored in encrypted form on secure servers. Participants will have access to the intervention for up to 12 weeks. dCBT-I will in effect be dCBT-I + TAU because there will be no requirement for participants (in either group) to alter their usual care in any way.

### Outcome measures

Our primary outcome will be *self-reported cognitive impairment*, assessed using the British Columbia Cognitive Complaints Inventory (BC-CCI) [32]. The BC-CCI comprises six questions scored using a 4-point scale (0–3 points; total score range: 0–18) probing perceived cognitive problems (with concentration, memory, and thinking skills) during the past 7 days. It was originally designed to probe cognitive complaints in those with depression – a disorder highly comorbid with insomnia, and sharing similar cognitive features [33]. Given the absence of a widely used measure of insomnia-related cognitive impairment the BC-CCI was selected based on good face validity, internal consistency data (Cronbach’s alpha = 0.82–0.86), and short (1-week) reference period.

### Secondary measures

*Objective cognitive performance* will be assessed through an online battery of tasks and will include measures of simple attention (*dependent variable [DV]: simple reaction time [msec] for correct identification of matching pairs [‘snap’]*), episodic memory (*DV: number of attempts to identify identical pairs of cards within a matrix)*, working memory (*DV: longest sequence of correctly recalled digits*), visual attention (*DV: time taken [secs] to link numbered circles*), and complex processing speed (*DV: number of correctly matched digit-symbols within a 2-min interval*). The battery was developed by the UK Biobank Cognitive Psychology Sub-Group for Cognitive Assessments. Prior to task commencement, participants are asked which text entry and pointing methods they will use to complete tasks (e.g. on full-sized keyboard, touchscreen, laptop trackpad or mouse).

#### Insomnia severity

Participants will complete the Insomnia Severity Index (ISI) [34] to quantify global insomnia severity. The ISI is a seven-item insomnia assessment tool, probing both nighttime and daytime aspects of insomnia disorder, and is sensitive to change following CBT-I. It is a recommended outcome measure in insomnia trials [35]. The ISI will be supplemented with four items from the Pittsburgh Sleep Quality Index (PSQI) [36] to permit calculation of quantitative sleep parameters, namely: total time in bed, sleep-onset latency, total sleep time, and *sleep efficiency*.

#### Fatigue

Fatigue will be assessed with the Multidimensional Fatigue Inventory (MFI) [37], a 20-item measure comprising five subscales; general fatigue, physical fatigue, mental fatigue, reduced motivation and reduced activity.

#### Sleepiness

Daytime somnolence will be assessed with the Epworth Sleepiness Scale (ESS) [38], an eight-item measure (score range: 0–24) probing propensity for ‘dosing’ in a range of daytime situations.

#### Cognitive failures

Self-reported cognitive failures will be assessed with the Cognitive Failures Questionnaire (CFQ) [39]. The CFQ comprises 25 questions scored using a 5-point Likert scale (range: 0–100) to identify frequency of minor cognitive mistakes over the past month.

#### Depression

Depressive symptoms will be measured using the nine-item (score range: 0–27) Patient Health Questionnaire (PHQ-9) [40].

#### Anxiety

Symptoms of anxiety will be assessed using two items [‘*Feeling nervous, anxious, or on edge’*, ‘*not being able to stop or control worrying’*; score range: 0–6] from the seven-item Generalised Anxiety Disorder 7 questionnaire (GAD-7) [41].

### Assessment of safety

The likelihood of serious adverse events occurring during this trial is low since CBT-I (in any format) has not been reported to cause them. The intervention offered in the trial has previously been tested in a randomised, placebo-controlled trial and no adverse outcomes were reported [20]. Since the trial is completed fully online, without formal participant contact, we are unlikely to become aware of potential adverse events. However, should we do so, we will define serious adverse events as: (1) death, (2) suicide attempt, (3) admission to hospital, and (4) formal complaints about the online intervention.

Studies have shown that daytime sleepiness and vigilance impairment may increase during Sleep Restriction Therapy (SRT) (one component of CBT-I), owing to restricted sleep opportunity. At the end of treatment (week 10), we will, therefore, ask participants to complete an adapted version of a previously used measure to assess differential rates of self-reported adverse effects [42].

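### Serious adverse events are picked up only passively and one of the four categories is in effect confined to the dCBT-I arm, so their counts cannot be compared between arms and a count of zero would not show absence of serious harm

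*Protocol article*

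**What the plan says.** The protocol article (Assessment of safety) has two separate safety streams.

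- **Serious adverse events.** The section explains: "Since the trial is completed fully online, without formal participant contact, we are unlikely to become aware of potential adverse events". It then defines the serious events to be recorded if the team does learn of any: "1) death, (2) suicide attempt, (3) admission to hospital, and (4) formal complaints about the online intervention".
- **Adverse effects.** Because sleep restriction may increase sleepiness and impair vigilance, participants will at week 10 "complete an adapted version of a previously used measure to assess differential rates of self-reported adverse effects". No restriction to one arm is stated.

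Three other places matter. Assessment points: "Assessments will take place at weeks 0 (baseline), 10 (post-treatment), and 24 (follow-up"). Sleepiness: "Daytime somnolence will be assessed with the Epworth Sleepiness Scale (ESS"). Depression: "Depressive symptoms will be measured using the nine-item (score range: 0–27) Patient Health Questionnaire (PHQ-9"). The secondary hypotheses in the Background compare sleepiness, depression and anxiety with wait-list at weeks 10 and 24. The Abstract fixes when the control arm gets the programme, and places the end of the controlled period at that same point: "At week 25, all participants allocated to the wait-list group will be offered digital CBT-I, at which point the controlled element of the trial will" (sentence cut here).

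**The concern.** Two features of the SAE stream work against its interpretation.

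First, the protocol does not ask about serious events; it waits for them to surface and says they probably will not. The recorded count then depends on who volunteers information as well as on what happened. That tendency may differ between arms, because participants know their allocation and only one arm is using the programme.

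Second, complaints about the programme are counted alongside death, suicide attempt and hospital admission. A complaint is not a clinical outcome. Wait-list participants have no access to the programme during the controlled period, so this category has in effect one arm to arise in.

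What is at stake is the later safety statement. The same section gives, as a ground for expecting low risk, that an earlier placebo-controlled trial of the programme reported no adverse outcomes. A report of no SAEs from this trial could be reused in the same way, although nobody had been asked.

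**Working it through.** **1. Is asking impossible because the trial is online?** The protocol attributes the gap to online conduct without formal contact. Against that:
- Both arms complete online assessments at weeks 10 and 24 (Assessment points).
- Participants are paid £10 and £15 for these two assessments (Participants).
- The trial coordinator monitors their completion (Blinding).
- The week-10 adverse-effects questionnaire already asks participants about harms online (Assessment of safety).

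Online conduct therefore does not prevent asking about hospital admission or suicide attempt.

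**2. Which categories can arise in which arm before week 25?**

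| Category | dCBT-I | Wait-list |
|---|---|---|
| Death | yes | yes |
| Suicide attempt | yes | yes |
| Hospital admission | yes | yes |
| Complaint about the programme | yes | in effect no |

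Three of the four categories can occur in both arms; the fourth is structurally unbalanced. The section states no counting window. Complaints from wait-list participants after week 25 are conceivable but fall outside the controlled period.

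**3. Does the week-10 measure fill the gap?** It is introduced because of sleepiness and vigilance. Nothing in the section says that it covers the listed serious events or that it is repeated at week 24. Programme access lasts up to 12 weeks (Intervention) and controlled follow-up runs to week 24, so part of both falls after its only stated use.

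**4. Numbers available.** The plan's own sample size reproduces. A two-sample t-test with standardised difference 0.42, two-sided 5% (sidedness assumed) and 90% power needs 121 per arm; 121 / (1 − 0.40) = 201.7, so 202 per arm and 404 in total.

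**5. What zero observed SAEs would mean.** With n participants, no events and complete capture, the upper one-sided 95% limit for the risk is 1 − 0.05^(1/n), or about 3/n.
- n = 202: 3/202 = 1.49% (exact 1.47%).
- With capture probability c, the limit for the true risk becomes about 1.49%/c.

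The protocol gives no value for c and expects it to be low, so no limit can be stated. If c differs between arms, the ratio of expected counts at equal true risk is c₁/c₀, which reflects ascertainment alone.

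**6. What asking would give.** With 40% attrition, 202 × 0.60 = 121 responders per arm. No events among them would give 3/121 = 2.48% (exact 2.45%). This holds only for responders, and only if they report every event.

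**7. What the week-10 measure can support.** With 121 responders per arm, two-sided 5% and 80% power, the detectable difference is about 13 points from an assumed control rate of 10%, 16 points from 20% and 18 points from 50%. That is enough for large differences in common self-reported effects, but not for rare serious ones.

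**The case against.** The strongest reply is that the protocol does plan a comparison of harms. The week-10 measure is meant for exactly that, and it answers the sleepiness concern which the section itself raises. Sleepiness, depression and anxiety are also compared between arms at weeks 10 and 24. **This stands.** A reader might infer from the SAE wording that the trial can support no statement on comparative safety at all; the documents do not bear that out. These are unblinded self-reports exposed to attrition, but they are comparative information on tolerability.

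Second, no between-arm SAE test is planned, there is no safety hypothesis, and the limitation is disclosed. This stands as far as it goes, and it lowers the weight of the point. Disclosure does not make the counts interpretable, however, and the remedy uses assessments that already exist.

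Third, a journal article condenses a fuller protocol, where SAE procedures usually sit. That would answer a complaint that procedures are missing. It does not answer this point, because the article itself states how events come to notice and what counts as serious.

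Fourth, a reader might infer that the whole SAE record is one-sided. It is not, since only the complaints category is. Separating it is partly a matter of labelling and could be done at reporting.

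Fifth, direct questions would not capture everything. People who have died cannot answer, and those who were admitted or attempted suicide may be less likely to respond. This stands and limits what the fix achieves.

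**Conclusion.** The point holds for serious adverse events only. By the protocol's own statement their ascertainment is passive, and one of the four categories is a non-clinical item in effect confined to the dCBT-I arm until week 25. SAE counts cannot be compared between arms, and an absence of recorded SAEs would not show absence of serious harm. The 1.5% limit for zero events in 202 requires complete capture, which the protocol expects not to have. No capture rate is given, so the shortfall cannot be quantified from the documents.

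The wider conclusion that nothing can be said on comparative safety is not supported. The week-10 measure and the sleepiness, depression and anxiety comparisons allow limited statements on tolerability. The content of the week-10 measure is not shown. If it already covers serious events, the gap narrows to the period after week 10 and to the complaints category.

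Neither the primary outcome nor any stated hypothesis is affected. This is a worthwhile, inexpensive improvement and not a flaw in the efficacy design.

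**What to change.** - Add the same brief questions to the week-10 and week-24 online assessments in both arms, asking about serious events since the last assessment: at least hospital admission and suicide attempt.
- Report the answers by arm with the number asked and the number answering, separately from events that came to notice by other routes.
- List complaints about the programme on their own, outside the clinical SAE count.
- State in the report that SAEs outside these questions were collected passively and that their counts are not compared between arms.

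**Cost.** A minor amendment, slightly longer surveys, and a procedure for handling positive answers, which is for the investigators and the ethics committee to set. Deaths and non-responders (40% allowed for in the sample size) would still be missed. Recruitment began on 18 October 2016 and was ongoing at publication, so participants already past week 10 when the change is made would have no week-10 answers. The denominators must show this.

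### Adverse effects are asked at week 10 with no stated baseline, so if the items record current symptoms, relief of existing complaints can mask new or worsened ones

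*Protocol article*

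**What the plan says.** The protocol article, under Assessment of safety, expects the team to hear of few adverse events because the trial runs online without formal participant contact. It then gives the reason for a dedicated questionnaire: "daytime sleepiness and vigilance impairment may increase during Sleep Restriction Therapy (SRT) (one component of CBT-I), owing to restricted sleep opportunity". The timing and purpose follow: at week 10, when treatment ends, participants are to fill in "an adapted version of a previously used measure to assess differential rates of self-reported adverse effects". No other systematic adverse-effect instrument is described.

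The Research design section schedules the primary and secondary variables at weeks 0, 10 and 24. The adverse-effect questionnaire is not listed among them in the Outcome measures and Secondary measures sections.

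Three other places bear on the point:

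- Background: "the most commonly cited areas of daytime dysfunction are problems with fatigue, work performance, cognitive functioning, and emotional regulation".
- Participants: an inclusion criterion is "endorsement of difficulties with concentration or memory using items from the Daytime Functioning and Sleep Attribution Scale".
- Background, secondary hypotheses: dCBT-I is expected to improve fatigue, sleepiness and cognitive failures, relative to wait-list, at weeks 10 and 24.

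**The concern.** The harms the questionnaire is meant to catch are close to complaints that participants bring into the trial and that the treatment is expected to relieve. If its items ask whether a symptom is present now, the week-10 rate in each arm is the sum of two parts: complaints that were there at baseline and have persisted, and complaints that are new. Successful treatment shrinks the first part in the dCBT-I arm only, and any harm enlarges the second. One measurement at week 10 gives only the total. A yes/no presence item also misses worsening of a complaint that was already present.

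At stake is how the safety result is read. A similar or lower rate on dCBT-I could be taken to mean that treatment brings on no extra complaints, when it may mean only that relief outnumbered new onset. An analysis plan written later cannot recover a baseline that was never collected.

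**Working it through.** **The plan's own figure.** The safety section gives no rate, sample size or power. The only figure to reproduce is the primary sample size, needed here for the number of completers. With a standardised difference of 0.42, 90% power and 5% significance (two-sided assumed), a t-test needs 121 per arm. Allowing for 40% attrition, 121/0.6 = 201.7, so 202 per arm and 404 in total, as stated. About 121 per arm are therefore expected to respond.

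**Model.** For one symptom let p be its baseline prevalence (equal in the arms by randomisation), r the proportion of existing cases relieved by week 10, and n the proportion of new cases among those without it at baseline.

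- Week-10 prevalence in an arm = p(1 - r) + (1 - p)n
- Difference, dCBT-I minus wait-list = (1 - p)(n_T - n_C) - p(r_T - r_C)
- Sign changes at p = (n_T - n_C) / [(n_T - n_C) + (r_T - r_C)]

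**Assumed inputs** (the documents give none): n_T = 25% and n_C = 10%, a 15-point excess among those at risk; r_C = 10%; r_T varied from 10% to 50%.

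**Worked case**, p = 50%, r_T = 40%:

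- dCBT-I: 0.5 × 0.60 + 0.5 × 0.25 = 42.5%
- Wait-list: 0.5 × 0.90 + 0.5 × 0.10 = 50.0%
- Difference: -7.5 points

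**Week-10 difference in points over the range:**

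| Baseline prevalence | r_T 10% | 20% | 30% | 40% | 50% |
|---|---|---|---|---|---|
| 0% | +15 | +15 | +15 | +15 | +15 |
| 20% | +12 | +10 | +8 | +6 | +4 |
| 40% | +9 | +5 | +1 | -3 | -7 |
| 50% | +7.5 | +2.5 | -2.5 | -7.5 | -12.5 |
| 60% | +6 | 0 | -6 | -12 | -18 |
| Sign changes above | never | 60% | 43% | 33% | 27% |

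In the first column relief is equal in both arms, and the difference is exactly the excess of new cases per participant: at 50% prevalence, 0.5 × 15 = 7.5. Masking therefore needs more relief on dCBT-I than on wait-list, which is what the secondary hypotheses predict.

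A second set of assumptions gives a similar picture. With relief of 50% versus 15% and the same onset rates, p = 50% gives 37.5% versus 47.5% (-10 points), p = 10% gives 27.5% versus 17.5% (+10 points), and the sign changes at 0.15/(0.15 + 0.35) = 30%.

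**Precision with a baseline.** At p = 50%, about 60 of 121 per arm are at risk, giving about 15 new cases (60.5 × 0.25) versus 6 (60.5 × 0.10). Power for 25% versus 10% with 60 per arm is 58%. The week-10 contrast of 42.5% versus 50.0% with 121 per arm has 21% power and points the other way. A baseline makes the harm visible but does not make the comparison well powered.

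**The case against.** The strongest reply is that the instrument is not shown. It is described as an adaptation of an earlier measure of adverse effects. If its items ask about symptoms that began or worsened since joining, the persistence term largely disappears, and most of the arithmetic with it. This stands, and it is why the point is conditional. Such wording would still rest on about ten weeks of recall by participants who know their allocation (Blinding section).

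Second, a reader might infer that the comparison is biased, or that its sign would be wrong. The documents do not support that. Randomisation makes the week-10 difference a valid estimate of the net effect on prevalence; in the worked case fewer dCBT-I participants really do have the symptom. What is lost is the separation of new or worsened complaints from relieved ones, which matters because benefit in some participants does not cancel harm in others.

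Third, a reader might infer that the named harms have no baseline at all, or that the protocol rules one out. Neither follows. The ESS, the MFI, simple reaction time and the PHQ-9 are measured at weeks 0, 10 and 24, and the Statistical analysis section plans for secondary outcomes an analysis analogous to the baseline-adjusted covariance analysis of the primary outcome. A net rise in mean sleepiness would be seen. But those analyses compare means, and a mean improvement can coexist with worsening in a subset; the article does not link these scales to safety. As to the questionnaire itself, the text states the week-10 use without saying that there is no other, and the schedule figure is not reproduced in the text available here.

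Last, every rate above is assumed. That stands too.

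**Conclusion.** The point holds in conditional form. The protocol states one administration of its only systematic adverse-effect measure, at week 10, and no baseline. It enrols people who already have related complaints and expects treatment to relieve them. If the items record current symptoms, the planned contrast measures net prevalence and cannot show an excess of new or worse symptoms separately. Relief in the dCBT-I arm can mask such an excess and, under some assumed rates, reverse its apparent direction.

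The size cannot be known from the documents. Under the tabulated assumptions a 15-point excess among those at risk shows as anything from +15 points (no baseline prevalence) to -18 points (60% prevalence, 50% relief). With equal relief in both arms there is attenuation but no reversal. The conclusion rests on the items recording current presence and on greater relief with dCBT-I. It is worth correcting because the remedy is cheap and the baseline cannot be recovered later; it does not touch the primary analysis.

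**What to change.** 1. Put the adverse-effect items, worded without reference to treatment so that both arms can answer, into the baseline survey before allocation, and repeat them unchanged at week 10.
2. Define the safety outcome for each symptom as new or worse than baseline, and compare its rate by arm.
3. Recruitment has begun, so participants already randomised will lack baseline items. For those not yet at week 10, ask at that assessment whether each symptom is new or worse since joining, and report them separately from those with a measured baseline. Anyone already past week 10 can contribute only through step 4.
4. From data already being collected, tabulate by arm the proportion whose ESS, MFI and PHQ-9 scores worsened from baseline at weeks 10 and 24, with the definition of worsening fixed before outcome data are examined. This complements the planned comparison of means.
5. If the adapted measure already asks about onset or worsening, say so in the protocol. Steps 1 and 4 would still reduce reliance on recall.

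The cost is a few more items in an existing online survey and one or two extra tables. The downsides are a slightly longer baseline survey, reliance on recall by unblinded participants among those already enrolled, and limited power for symptoms that are common at baseline. Sample size and primary analysis are unchanged.
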